### Recruitment, retention and withdrawal of participants

#### Inclusion criteria

The inclusion criteria for ENDIA are an unborn child with an FDR with T1D, targeting the mother for recruitment in first, second or third trimester of pregnancy, or an infant less than six months of age with a FDR with T1D.

#### Exclusion criteria

The only exclusion criterion is the incapacity for the pregnant woman (or in the case of postnatal recruitment, the child’s primary caregiver) to understand the requirements of her and/or her child’s participation. This may be due to illiteracy, an intellectual disability or a mental illness.

#### Withdrawal criteria

Participants will be withdrawn from the study if they develop T1D in the case of the child, or request to discontinue participation in the case of the mother on behalf of herself and the child. The reason for withdrawal from the study will be captured on the case report form. Every effort will be made to continue to follow all participants enrolled in the study except for those who withdraw consent. Participants who are withdrawn from the study will be contacted by telephone annually to determine their T1D status.

#### Recruitment

Participants will be identified during pregnancy or within six months of birth in NSW, WA, Qld, Vic and SA. FDRs will be mothers, fathers or siblings with T1D. Since majority will be a mother or a father with T1D, pregnant women with T1D or whose partner has T1D are the main focus of recruitment. Eligible participants will be identified from the following sources: (1) prospective mothers attending public and private antenatal clinics prior to delivery, (2) prospective parents attending public and private diabetes clinics, (3) pregnant mothers of existing patients attending paediatric diabetes clinics, (4) diabetes organisations, and (5) local and national mainstream advertising.

Private endocrinologists and obstetricians known to manage T1D in young adults will be targeted with visits from research staff and personalised letters, brochures and posters. Paediatric T1D clinics will recruit families in which a sibling has T1D. Our research team includes endocrinologists and a perinatologist, all with substantial experience in recruitment of participants during pregnancy.

State and national diabetes networks and advocacy groups will be used to promote the study, as well as a dedicated website (http://www.endia.org.au) and social media such as Facebook (https://www.facebook.com/endiastudy) and Twitter. All advertising material, media releases and other articles intended for the general public will be approved by the relevant Human Research Ethics Committees in each state prior to distribution.

#### Participant retention

Our past experience indicates that families affected by T1D are highly motivated to participate in research. The previous Australian BabyDiab birth cohort in SA and Victoria recruited 548 children followed over a median of 5.7 years, while the participant retention rate in the NSW arm of the TRIGR study was 87% after five years (80% planned) [93]. This high rate is attributed to frequent family phone contacts, newsletters, distribution of calendars with reminders and incentives such as birthday cards, the set-up of parent’s groups for T1D families and active assistance with surveillance of the health of the participating child. Similar strategies will be implemented in ENDIA.

Participant engagement in the study will be central to high retention rates. More than half of people within the target population (men and women aged 18–34) have a Facebook page [102]. The site will be monitored daily and updated regularly to maintain relevancy. We will also use Facebook to link with existing T1D networks and advocacy groups, including JDRF International, JDRF Australia and Diabetes Australia, thereby generating further awareness of the study.

### Study activities

#### Pregnancy visits 1 and 2: first and second trimesters

The following will be undertaken before 13 weeks gestation and again before 26 weeks gestation:

• Documentation of maternal and paternal demographics including medical and obstetric history

• Maternal anthropometry: height, weight, BMI

• Collection of blood sample for investigations defined in Table 1

• Collection of nasal, buccal, tongue and throat swabs, urine and stool specimens for microbiome studies

• Administration of the Pregnancy Lifestyle Questionnaire and Pregnancy Physical Activity Questionnaire [96]

• Documentation of proband history of T1D and other significant medical history

• Blood and saliva will also be collected from the proband on one occasion for HLA genotyping and SNP analysis, respectively

#### Pregnancy visit 3: third trimester

Between 24 and 38 weeks gestation investigations will be as for first/second trimester PLUS

• Documentation of results of the oral GTT, as routinely performed in pregnancy

• Explanation by research nurse (trained by study dietician) as to how to complete the DQES version 2 (DQESv2) questionnaire for nutrition analysis [95]

• Vaginal and skin swabs for analysis of the microbiome

• Documentation of pregnancy complications: hypertension, preeclampsia, HELLP, hyperemesis gravidarum

#### Birth and week 1 of life

The following will be undertaken across two study visits within the first week of life. The first, termed the B1 visit, will be within the first two days post-partum; the second, termed the B2 visit, will be 3–5 days post-partum.

• Collection of cord blood samples for investigations defined in Table 1

• Completion of the documentation of the pregnancy complications, and /or of any congenital abnormalities in the child

• Documentation of birth date, gestation, gender, birth weight, placental weight, birth length, APGAR score, method of delivery and any complications of the birth, perinatal and neonatal periods

• Record of maternal weight gain during pregnancy

• Viral studies, including serology and qPCR, will be performed from urine taken at B2 visit

• Collection of colostrum samples at B1 and B2 visits for microbiome studies

• Collection of skin swabs from infant and mother B1 and B2 visits for microbiome studies

• Collection of meconium (first nappy) at B1 visit and stool samples, nasal, buccal, tongue and throat swabs from infant at B2 visit, all for microbiome studies

#### Follow-up visits at 3, 6, 9, 12, 15, 18, 21, 24, 30 and 36 months of age

The following will be performed once:

• Saliva sampling from the infant for SNP genotype

• Documentation of maternal nutrition during lactation using the DQESv2 questionnaire at three months

The following will be undertaken at each visit:

• Collection of blood sample for investigations outlined in Table 1. If a child develops persistent islet autoimmunity, as defined above, HbA1c will be also measured 6-monthly

• Anthropometrics: length (height at 30 and 36 months), weight, BMI, waist circumference (at umbilicus)

• Collection of nasal, buccal, tongue, throat and skin swabs and stool samples for microbiome studies

• Nutrition and Lifestyle assessments (Refer to Additional file 1)

### Data collection, sampling procedures and laboratory investigations

A detailed description of the data collection, sampling procedures and laboratory investigations can be found in Additional file 1. Data collection tools developed specifically for the ENDIA Study evaluating infant feeing, maternal lifestyle in pregnancy, and maternal/infant lifestyle postpartum are provided in Additional files 2, 3 and 4, respectively.

### Analysis of the primary outcome measure

The primary outcome measure is islet autoimmunity defined as elevation of ≥ one islet autoantibody on consecutive tests. Time-to-event analyses will explore the effect of variables on the risk of islet autoimmunity. Unadjusted and adjusted Hazard Ratios (HR) will be calculated using parametric and non-parametric (proportional hazard) survival models. The models will account for right censored data due to variable length of follow up and loss of follow up of participants. Variables measured over time (continuous and categorical) will be entered into survival models as time-dependent covariates as these measurements will be repeatedly obtained from individual participants. Adjusted HRs will be used to analyse the development of islet autoimmunity while controlling for associated variables as we have described [12]. Viral infections will also be modelled using survival analysis techniques. A fixed (time-independent) covariate will be used to test for associations with antenatal/postnatal viral infections/events, and time-dependent variables will be constructed to indicate exposure to viral infections throughout the follow-up period for each child.

Logistic regression analysis will be used to compare the relationship between presence or absence of islet autoimmunity and other variables. For analysis of nested case controls and longitudinal changes in the microbiome, islet autoimmune and non-islet autoimmune participants will be matched for age, gender, HLA type, ethnicity, proband relationship, parity, mode of delivery and gestation/birth weight.

A systems biology approach will be used to reveal inter-relationships between prenatal and postnatal environmental exposures that may condition the microbiome, metabolome and epigenome – these include maternal T1D, nutrition, weight gain, physical activity and viral infection during pregnancy; and mode of delivery, accelerated weight gain, nutrition, immune function, early fever, antibiotic use and viral infection during early life.

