### Hypothesis and objectives

#### Hypotheses

The unifying hypothesis is that gene-environment interactions during prenatal and postnatal development drive the development of islet autoimmunity and T1D in children at-risk for T1D.

The specific hypotheses are:

1. The maternal microbiome during pregnancy and lactation differs in composition, diversity and functional products between mothers whose offspring do and do not develop islet autoimmunity and T1D.

2. The microbiome differs in composition, diversity and functional products in children who do and do not develop islet autoimmunity and T1D during the first three years of life.

3. Accelerated weight gain during pregnancy, and accelerated weight gain and insulin resistance during the first three years of life, is associated with an increased risk of islet autoimmunity.

4. Viral infection during pregnancy and first three years of life modifies the risk of islet autoimmunity and T1D.

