### Determination of sample size

We estimate recruitment of 1,400 participants from the five states over three years, followed for a median of two years with a 9% rate of persistent islet autoimmunity. Maximum total dropout /lost to follow-up rate is estimated at 15% with the majority of dropouts occurring in the first six months of follow-up. These estimates are based on data from the Australian BabyDiab [12] and TRIGR [93] at-risk birth cohorts in which dropout rates were 15% and 7%, respectively.

Using nQuery Advisor, with 600 participants above the median and 600 below (1200 total after 15% drop out from 1,400), for a given exposure variable, power is 90% to detect a difference between survival (i.e. no islet autoimmunity) of 93% in one group and survival of 88% in the other – with 108 events (islet autoimmunity) or 9% of the total sample of 1,200 required [101]. For examining interactions between uncorrelated exposure variables with approximately 375 participants per combination of above/below the median, the power is 77% to detect a difference in survival (no islet autoimmunity) between 93% and 87% (70 events in 600 participants required).

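### The fixed covariate for viral infection is not limited to exposure known at birth; depending on its coding, the postnatal part is open to immortal-time bias or attenuation, and no model is named as primary.

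*Protocol article*

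**What the plan says.** In the protocol article, the section on analysis of the primary outcome measure gives two codings for viral infection in one sentence. The first is: "A fixed (time-independent) covariate will be used to test for associations with antenatal/postnatal viral infections/events". The second is: "time-dependent variables will be constructed to indicate exposure to viral infections throughout the follow-up period for each child". Earlier the same section sets a general rule: "Variables measured over time (continuous and categorical) will be entered into survival models as time-dependent covariates".

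Hypothesis 4 gives the exposure period: "Viral infection during pregnancy and first three years of life modifies the risk of islet autoimmunity and T1D". Table 1 schedules virology on blood, stool and throat samples at the visits from 3 to 36 months, so postnatal infection is measured repeatedly during follow-up. The article does not define the exposure window of the fixed covariate, and it does not say which of the two codings answers hypothesis 4.

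**The concern.** A fixed covariate classifies a child from the start of follow-up. That suits an exposure complete at birth. For an infection at, say, 14 months, the child is placed in the exposed group from birth on the strength of something that happens later. If infections count only up to the event or censoring, a child has to stay free of islet autoimmunity long enough to be infected. The event-free months before infection are then credited to the exposed group, which is immortal-time bias. If infections after seroconversion also count, the outcome can precede the exposure, and uninfected time is mixed into the exposed group.

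Either way, the fixed and time-dependent models can give different answers to hypothesis 4, possibly in opposite directions. The text leaves open which would be reported as the result.

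**Working it through.** **The plan's own figure.** The article gives no figure for the viral analysis. Its figure for the primary time-to-event comparison is 108 events with 90% power, from "Using nQuery Advisor, with 600 participants above the median and 600 below" and event-free proportions "of 93% in one group and survival of 88% in the other".
- Events: 0.09 × 1,200 = 108.
- Implied hazard ratio: ln(0.93)/ln(0.88) = 0.568, or 1.76 inverted.
- Schoenfeld power: Φ(√(108 × 0.25) × |ln 0.568| − z) = Φ(2.942 − z). This is 90.3% with z = 1.645 and 83.7% with z = 1.960. The stated power therefore corresponds to a one-sided 5% test. The article states neither alpha nor sidedness, and nothing below depends on it.

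The HR of 0.568 serves here only as a yardstick for the size of the bias.

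**Inputs for the check.**
- From the article: "followed for a median of two years with a 9% rate of persistent islet autoimmunity", and an odds ratio of about 4 for enterovirus and islet autoimmunity (background section on viral infection), used as an illustrative true HR.
- Assumed: follow-up uniform from 0.5 to 3.5 years (median 2), constant event hazard set to give 9% events, constant infection rate r per child-year, and a Cox model with one covariate. The article gives no infection rate, so a range is shown.

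**Null case, infection counted if before event or censoring.** If a proportion p is infected by two years, r = −ln(1 − p)/2. For p = 20%, 50% and 80%, r = 0.112, 0.347 and 0.805 per year. With a true HR of 1, the simulated fixed-covariate HR is about 0.47, 0.38 and 0.25 (0.46, 0.38 and 0.25 in a repeat run). All three lie further from 1 than the 0.568 that the study is sized to detect.

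**Three possible fixed codings and the time-dependent coding.** These come from simulated cohorts of 600,000 children, made large to remove sampling noise. A = infected before event or censoring. B = infected at any time in follow-up, including after seroconversion. C = infected in the first 3 months. TD = time-dependent.

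| r per year | A, true 1 | A, true 4 | B, true 1 | B, true 4 | C, true 1 | C, true 4 | TD, true 1 | TD, true 4 |
|---|---|---|---|---|---|---|---|---|
| 0.1 | 0.47 | 1.76 | 1.00 | 2.43 | 1.00 | 3.00 | 1.01 | 4.06 |
| 0.25 | 0.40 | 1.52 | 1.00 | 2.51 | 1.00 | 2.43 | 1.02 | 3.99 |
| 0.5 | 0.33 | 1.24 | 1.01 | 2.55 | 1.00 | 1.98 | 1.01 | 4.06 |
| 1 | 0.21 | 0.76 | 1.01 | 2.67 | 1.00 | 1.58 | 0.99 | 4.02 |
| 2 | 0.10 | 0.33 | 1.01 | 2.94 | 1.00 | 1.32 | 1.01 | 3.94 |
| 4 | 0.03 | 0.10 | 0.95 | 3.97 | 1.02 | 1.18 | 1.00 | 4.10 |

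**Sensitivity: no events before 6 months.** Coding A gives 0.57 down to 0.09 when the true HR is 1, and 2.18 down to 0.34 when it is 4; in the second case the estimate falls below 1 only from 2 infections per year. Coding B gives about 2.8 to 3.7 for a true HR of 4 at rates of 0.1 to 2.

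**Reading the table.** Coding A biases the null strongly at every rate. Coding B keeps the null but attenuates a true effect at rates up to 2 per year. Coding C keeps the null and dilutes a true effect, increasingly so as infection becomes common, because children infected later sit in the unexposed group. Only the time-dependent coding recovers the truth throughout.

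**The case against.** The strongest reply is that the valid method is already planned in the second half of the same sentence and in the section's general rule. One can read the sentence as a division of labour, with a fixed covariate for events around birth and time-dependent variables for the rest. The birth-week section does place viral studies at 3 to 5 days post-partum, so an early measurement suited to a fixed covariate exists. A condensed article may also leave the exact window to a fuller document.

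Part of this stands. A reader might infer that the plan would necessarily make infection look strongly protective, or that hypothesis 4 has only an invalid analysis. The documents support neither. The protective artefact under the null appears in only one of the three fixed codings tested. Coding B is feasible too, because under the withdrawal criteria a child leaves at T1D and not at seroconversion. Even under coding A, a true HR of 4 stays above 1 at rates up to 0.5 per year. Banning every fixed postnatal covariate would also go too far, since a short early window leaves the null intact.

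What does not stand is the idea that this is merely omitted detail. The article states the fixed coding for postnatal infection without restriction, against its own rule for variables measured over time, and with a hypothesis that runs to three years. Planning both models does not resolve the matter while neither is primary.

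**Conclusion.** The concern holds in conditional form. As written, the fixed covariate extends to exposure that accrues during the time at risk. It permits a coding under which no effect appears as an HR of about 0.47 to 0.25 (20% to 80% infected by two years) and a true HR of 4 appears anywhere from 1.76 to 0.10 (0.1 to 4 infections per year). It also permits a milder coding that keeps the null but shrinks a true HR of 4 to about 2.4 to 2.9 at 0.1 to 2 infections per year.

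These sizes rest on the assumed infection rates, constant hazards and the follow-up distribution; the direction of the null bias under coding A held at every rate tried, with and without early events. The issue affects one of four specific hypotheses and leaves the sample-size calculation untouched. It should be settled before the viral data are analysed.

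**What to change.** Reword the viral-infection sentence to do three things:

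1. Limit the fixed covariate to antenatal infection and infection detected at birth. Alternatively, limit it to a prespecified early window, with follow-up for that analysis starting at the end of the window (a landmark analysis).
2. Analyse all later postnatal infection only through the time-dependent variables, each switching from unexposed to exposed at the first positive sample.
3. Name the time-dependent model as primary for hypothesis 4.

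Lagging exposure by one visit, so that an infection found at the seroconversion visit is not counted as preceding it, can be a sensitivity analysis.

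The cost is one sentence and no new data, since the time-dependent variables are already planned. The landmark option would drop the few events that occur before its window ends.

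### Logistic regression on presence or absence of islet autoimmunity has no fixed age, follow-up term or restriction to the matched sets, so its odds ratios can be biased where exposure is tied to length of follow-up

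*Protocol article*

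**What the plan says.** In the protocol article, the section Analysis of the primary outcome measure opens with survival methods: "Time-to-event analyses will explore the effect of variables on the risk of islet autoimmunity". It recognises unequal observation and deals with it inside those models: "The models will account for right censored data due to variable length of follow up and loss of follow up of participants". Repeated measurements are treated likewise: "Variables measured over time (continuous and categorical) will be entered into survival models as time-dependent covariates". Viral infections are also assigned to survival techniques, with both fixed and time-dependent terms.

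The next paragraph adds a second method for the same outcome: "Logistic regression analysis will be used to compare the relationship between presence or absence of islet autoimmunity and other variables". The sentence after it introduces nested case-control and longitudinal microbiome analyses, in which autoimmune and non-autoimmune "participants will be matched for age, gender, HLA type" and further factors. No model is named for those sets, and the logistic sentence is not tied to them.

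Determination of sample size gives the follow-up pattern: "We estimate recruitment of 1,400 participants from the five states over three years, followed for a median of two years". It assumes a 9% rate of persistent autoimmunity and at most 15% loss, most of it in the first six months.

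**The concern.** Under staggered entry and loss, absence of autoimmunity means different things for different children. One child may have been observed for a few visits and another to 36 months, yet a logistic model without a follow-up term counts both as equally event-free. The section solves this problem for the survival models and then commits to a model in which it is not solved.

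Two situations make this matter. The first is an exposure whose frequency differs by recruitment date or by dropout, because it is then associated with time at risk. The second is an exposure that builds up during follow-up, such as fever or antibiotic use, because the chance of being recorded as exposed also depends on observed time. In either case the odds ratio can depart from one with no true effect, or a true effect can be hidden, and the odds ratio and hazard ratio for the primary outcome can disagree.

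**Working it through.** **Inputs from the article.** 1,200 children analysed (600 per exposure group), 9% autoimmunity, median follow-up two years, recruitment over three years, autoimmunity-free survival 93% versus 88%.

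**Assumptions.** Constant hazard; 9% reached at two years; follow-up uniform from 0.5 to 3.5 years unless stated (a three-year spread centred on the stated median). The article gives neither the spread nor any link between exposure and follow-up.

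**The plan's own figure.** HR = ln 0.88 / ln 0.93 = 1.76. Schoenfeld power with 108 events is Φ(½·√108·ln 1.76 − z) = Φ(2.94 − z). This is 90.3% at one-sided 0.05 and 83.7% at two-sided 0.05. The stated 90% therefore reproduces on a one-sided test; the article states no alpha or sidedness. The present point does not depend on this figure. It only supplies the rates.

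**Step 1: how much follow-up matters.** Hazard λ = −ln(0.91)/2 = 0.0472 per year. The chance of being recorded positive is 1 − exp(−λt): 2.3% at 0.5 years and 15.2% at 3.5 years.

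**Step 2: fixed exposure unrelated to follow-up.** 600 simulated cohorts per scenario:
- True HR 1.76: logistic OR 1.79, Cox HR 1.75.
- No effect: OR 0.99, 4.3% rejections.

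There is almost no bias.

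**Step 3: exposure related to recruitment time, no true effect.** Earlier recruits are followed 2 to 3.5 years and later recruits 0.5 to 2 years. The average risk over an interval (a, b) is 1 − [exp(−λa) − exp(−λb)] / [λ(b − a)], which gives 12.14% for earlier and 5.70% for later recruits.
- Exposure in 65% of earlier and 35% of later recruits: exposed 0.65 × 12.14 + 0.35 × 5.70 = 9.89%; unexposed 0.35 × 12.14 + 0.65 × 5.70 = 7.96%. OR = (0.0989/0.9011) / (0.0796/0.9204) = 1.27.
- 60%/40%: 9.57% versus 8.28%, OR 1.17.

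Two sets of simulations agree: OR 1.26 to 1.27 with about 21% false positives, and 1.15 to 1.18 with 10% to 11%. Cox HRs in the same scenarios were 1.00 (6% rejections) and 0.98 (4.3%).

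**Step 4: mean follow-up differs directly by exposure.**

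| Scenario | Logistic OR (rejections) | Cox HR (rejections) |
|---|---|---|
| No effect, 2.25 vs 1.75 years | 1.31 (24%) | 1.00 (3.8%) |
| No effect, 2.5 vs 1.5 years | 1.71 (73%) | 1.00 (5.5%) |
| True HR 1.76, exposed 1.5 vs unexposed 2.5 years | 1.05 (4.7%) | 1.77 (81%) |

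In the last row the logistic model loses the design effect almost entirely. A complementary log-log model with log follow-up as offset matched Cox in all of these fixed-exposure scenarios.

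**Step 5: exposure accruing during follow-up, no true effect, half exposed by two years.**
- Coded as ever exposed by the end of follow-up: OR 1.31.
- Coded as exposed before the event or censoring: OR 0.48.
- Time-dependent rate ratio: 0.99.

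With faster accrual (0.7 per year) the three figures are 1.52, 0.41 and 1.01. The direction depends on coding.

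**The case against.** The strongest defence is that the logistic sentence stands immediately before the sentence on age-matched nested case-control sets, apart from the survival paragraph, and logistic regression is the usual tool for such sets. Nothing in the text says that the model is unconditional, so it would be wrong to infer that the plan has chosen the wrong model for matched data. That stands. But matching is introduced only for a separately named analysis, and nothing confines the logistic regression to it.

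A reader might also infer that the logistic results must be biased, or must lean towards protection. The documents support neither. Bias needs exposure to be related to follow-up, or to be coded over it. The article reports no such relation, and the splits and follow-up differences above are illustrations. For accruing exposures the sign depends on coding.

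Repeated measures and viral infections are already assigned to survival models. This narrows the reach of the problem but does not exclude other early-life exposures from the logistic analysis. The hazard ratios come first in the section and are unaffected.

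Finally, an article may leave an age horizon or control sampling to the full protocol or the SAP. True, and their absence alone would be no finding. The point here is a method that the article does state, for the primary outcome and without limit, next to its own acknowledgement of variable follow-up.

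**Conclusion.** The point holds as a conditional one. As written, the logistic regression can be applied to the whole cohort with unequal time at risk. For a fixed exposure unrelated to follow-up this does almost no harm. Where exposure tracks recruitment time, a modest imbalance gives a null odds ratio of about 1.15 to 1.27 with 10% to 21% false positives; for accruing exposures the null odds ratio is about 0.5 or 1.3 according to coding. These sizes rest on an assumed constant hazard, an assumed 0.5 to 3.5 year follow-up spread and assumed exposure patterns. They show what could happen and do not predict what will.

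It would go too far to say that the primary analysis is compromised: the time-to-event models handle the problem, and the weakness is confined to the added logistic analysis. The change is worth making because it costs little and prevents conflicting odds and hazard ratios for the same outcome.

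**What to change.** State that the time-to-event models are the sole basis for cohort-wide inference on islet autoimmunity. Then give logistic regression one defined, supportive role:

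- **Matched nested case-control sets:** conditional logistic regression, with controls still under follow-up and autoantibody-negative at the case's age at seroconversion; or
- **A fixed-age outcome:** autoimmunity by a stated age, with inverse-probability weighting for loss before that age; or
- **Replacement** by a complementary log-log model with log length of follow-up as offset. This was checked here for fixed exposures only; accruing exposures should stay in the survival models as time-dependent covariates.

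The cost is analysis wording and slightly more analysis work. Design, sample size and data collection do not change. A fixed-age analysis loses some children: with a median of two years (if counted from birth), a two-year horizon would be reached by only about half of them.
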